### Study outcomes and data analysis

The primary outcome is the percentage reduction in the depth and duration of FHR deceleration in the intervention group compared with the control group. Secondary outcomes include foetal, neonatal and maternal outcomes.

#### Foetal outcome

*FHR changes*: Changes in specific features of the CTG, including the following:Decelerations with loss of internal variability (beat-to-beat variability of < 5 beats per minute [bpm])Decelerations in combination with tachycardia of bradycardia (> 160 or < 110 bpm)Unassignable baselinePhase-rectified signal averaging (PRSA), a relatively new technique used to determine FHR variability by estimating the accelerative capacity (AC_PRSA_) and decelerative capacity (DC_PRSA_) of the foetal heart. This technique is explained in articles by Bauer and Huhn [62, 63].*Change in modified FIGO classification* (Table 1) [60, 61].

In the next subsection, methodology regarding the comparison of FHR tracings and timeframes is described in more detail.

#### Neonatal outcome

Neonatal outcome includes Apgar score, NICU admission, venous and arterial umbilical cord blood gas analysis (pH, lactate, base excess, pO_2_ and pCO_2_) and malondialdehyde (MDA, a marker for free oxygen radical production) in arterial and venous umbilical cord blood. Information on neonatal admission is a standard part of the maternal hospital chart. Determination of 1- and 5-minute Apgar scores and venous and arterial umbilical cord blood gas analysis (pH, lactate, base excess, pO_2_ and pCO_2_) is common practice. Cord blood gas analysis will be performed immediately after birth using the ABL 90 flex blood gas analyser (Radiometer Benelux BV, Zoetermeer, The Netherlands) with both venous and arterial cord blood. Two additional blood samples (one venous and one arterial sample) are drawn from the umbilical cord in heparinised tubes and immediately centrifuged and stored at the laboratory of Máxima Medical Centre at − 20 °C. Once all samples are collected, they will be transported to the Laboratory of Genetic and Metabolic Diseases of the Academic Medical Centre Amsterdam (Amsterdam, The Netherlands), where total (free and bound) MDA will be determined as the 2,4-dinitrophenylhydrazine (DNPH) derivative. A stable isotopically labelled analogue (^2^H_2_-MDA) will be added as an internal standard, then alkaline hydrolysation, deproteinisation and derivatisation with DNPH, and MDA-hydrazone will be analysed by high-performance liquid chromatography-tandem mass spectrometry and positive electrospray. Samples will be injected on a SUPELCOSIL LC-18-DB analytical column (250 × 4.6 mm, 5-μm particles; Sigma-Aldrich, St. Louis, MO, USA) and will be separated using an ACQUITY ultra performance liquid chromatography system (Waters, Milford, MA, USA). Samples will then be analyzed by a Quattro Premier XE mass spectrometer (Waters, Milford, MA, USA). Analytes and internal standards will be eluted with acetonitrile/water/acetic acid (50/50/0.2) and detected in multiple reaction monitoring mode for the transitions of mass-to-charge ratio (*m/z*) 235 → *m/z* 159; *m/z* 237 → *m/z* 161.

#### Maternal outcome

Maternal outcome measures include the mode of delivery, side effects and reasons for discontinuation of oxygen administration. Side effects include headache, dizziness, discomfort of the non-rebreathing mask and any other complaint mentioned by the participant. The delivery room staff will register on the case report form if the parturient experiences any side effects and/or if there are reasons for eventual discontinuation of oxygen administration. Also, to gain insight into how labouring women experience receiving additional oxygen via a non-rebreathing mask compared with receiving normal care, a short questionnaire will be used to investigate experiences of all the participants with this study.

### Analysis of outcome measures regarding FHR pattern

#### Changes in FHR pattern

The digital CTG tracings will be extracted from CS-EZIS (ChipSoft, Amsterdam, The Netherlands) and analysed using MATLAB 2015a software (MathWorks Inc., Natick, MA, USA). For the computerised CTG analysis, we will use a custom-made algorithm based on the OxSys system [64] that will first be validated by an expert panel. This expert panel will also manually classify the CTG into one of the FIGO categories [60, 61]. Regarding the analysis of specific CTG features, we searched the literature for CTG features that are likely related to neonatal outcome. A large variety of CTG features have been investigated in relation to neonatal outcome, with varying results. However, three features are consistently mentioned as being related to neonatal outcome: decelerations with loss of internal variability, decelerations in combination with tachycardia or bradycardia and periods with unassignable baseline [3, 60, 64–71]. Besides, AC_PRSA_ and DC_PRSA_ turned out to predict acidaemia better than short-term variation [62, 72, 73]. We therefore include this parameter as an outcome measure.

#### What is the time frame of interest?

All patients serve as their own control, with changes in FHR being compared before and after the start of the study protocol, regardless of whether the patients belong to the control or the intervention group. Results in the intervention group and the control group will also be compared.

For the analysis where patients serve as their own control, the time frames of interest for outcomes related to changes in FHR are as follows:*Control group*: 10 minutes before and after the start of the study protocol. In total, 20 minutes of data will be analysed (Fig. 2).*Intervention group*: 10 minutes before the start of the study protocol up to 15 minutes after the start of the study protocol. The time frame of interest after the start of the study protocol is determined as the period between 5 and 15 minutes after maternal hyperoxygenation is initiated, motivated by the expectation that it will take 5 minutes for maternal pO_2_ to increase to a maximum of approximately 475 mmHg [24]. After that, the effect of the intervention will be observed for 10 minutes. In total, 20 minutes of data will be analysed (Fig. 3).

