### Statistical analysis

#### Sample size calculation

The study consists of two study groups: one group with suboptimal FHR patterns and one group with abnormal FHR patterns. We aim for the study to have 80% power and a level of significance of 0.05 in both groups. In one small, non-randomised study, a reduction in FHR decelerations (type II dips) of 50–100% was noted. Our present study is the only one to report FHR changes as a result of maternal hyperoxygenation. On the basis of available literature, we expect ≥ 50% improvement in the oxygen group and 0% in the control group in both suboptimal and abnormal FHR patterns [28]. We estimated a mean improvement of 50% with an SD of 50% in each group. A power analysis performed in G*Power 3.0.10 (Kiel University, Kiel, Germany) for a two-tailed Mann-Whitney *U* test (assuming that data will not be equally distributed) resulted in a sample size of 67 patients in each study group. We added an extra 20% to compensate for missing data. Because we have two separate study groups (suboptimal and abnormal FHR group), we need 162 patients to participate.

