#### Data analysis

IBM SPSS Statistics software (version 24; IBM, Armonk, NY, USA) will be used to perform statistical analysis of the study results. Assuming non-normal distribution, the primary clinical outcome will be analysed with a Mann-Whitney *U* test for differences between the intervention and control groups and a Wilcoxon matched-pairs test for changes within the same participant. When outcome data are found to be normally distributed, independent samples *t* tests (two-tailed) will be used to analyse differences between the intervention and control groups, and paired *t* tests will be used for changes within the same participant. Outcome measures will be calculated for the combined group and the subgroups of suboptimal and abnormal FHR tracings, as well as for small for gestational age (SGA, lower than 10th percentile) and appropriate for gestational age (AGA) neonates. In the intervention group, oxygen may not be applied, owing to practical concerns such as very quick progression of labour. Therefore, we will perform both per-protocol and intention-to-treat analyses. In the per-protocol analysis, parturients who actually received oxygen will be compared with those who did not receive oxygen. In addition, unjust inclusions will be excluded from this analysis.

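### The oxygen arm's FHR window is timed from oxygen initiation, so intention-to-treat leaves women who never receive oxygen without a defined primary-outcome window, and fast labours lose data unequally between arms

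*Protocol article*

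**What the plan says.** All references are to the protocol article.

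- **Study outcomes and data analysis** sets the endpoint in one sentence: "The primary outcome is the percentage reduction in the depth and duration of FHR deceleration in the intervention group compared with the control group". A percentage reduction needs a before period and an after period.
- **What is the time frame of interest?** The windows are introduced with the words "For the analysis where patients serve as their own control, the time frames of interest for outcomes related to changes in FHR are as follows". Controls are measured "10 minutes before and after the start of the study protocol". The oxygen arm has an overall frame of "10 minutes before the start of the study protocol up to 15 minutes after the start of the study protocol", but its after period is then fixed as "the period between 5 and 15 minutes after maternal hyperoxygenation is initiated". The 5-minute lag is justified by the time maternal pO2 is expected to need to reach its maximum. The section adds that the two groups' results will be compared.
- **The text following Fig. 3** defends these periods as the ones in which hyperoxygenation can be set against no treatment. It adds a further comparison from the start of the study until birth, with a caution about other interventions.
- **Data analysis** foresees non-receipt: "In the intervention group, oxygen may not be applied, owing to practical concerns such as very quick progression of labour". For that reason the plan promises an intention-to-treat analysis alongside a per-protocol one.
- **Sample size calculation** makes an allowance for lost outcomes: "We added an extra 20% to compensate for missing data".

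**The concern.** In the oxygen arm the clock for the after period starts at an event that follows randomisation, that has no counterpart in the control arm, and that the plan itself expects sometimes not to occur. The reason given for its not occurring is rapid labour, which is plausibly related to the FHR trace. The women who make an intention-to-treat analysis necessary are thus the ones for whom the written rule supplies no outcome.

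If they drop out of the comparison by default, or are handled by a rule devised after the data are seen, the remaining oxygen-arm women are a selected group and the controls are not selected in the same way. The 20% added to the sample size restores numbers but does not correct selective loss.

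**Working it through.** The plan gives no figure on this point to reproduce: it states neither times from randomisation to birth nor a rate of oxygen not being given. The check is a comparison of the passages, followed by an illustration on stated assumptions.

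**Step 1. Which moment is time zero in the oxygen arm?** The overall frame ends 15 minutes after the start of the study protocol. The after period ends 15 minutes after oxygen initiation. The two agree only if those are the same moment, so the article treats them as one event. For a woman who never receives oxygen they cannot be.

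**Step 2. What does each woman contribute?**

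| Situation | Oxygen arm, clock from oxygen initiation | Oxygen arm, clock from start of protocol | Control arm |
|---|---|---|---|
| Oxygen never given | No window defined | 5–15 min | Condition does not arise |
| Birth before minute 5 | No post-start data | No post-start data | Partial 0–10 min window |
| Birth at 5–10 min | Partial window | Partial window | Partial window |
| Birth at 10–15 min | Partial window | Partial window | Full window |

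For the birth rows in the first oxygen column, oxygen is taken to start at time zero. Any delay makes that column worse. The arms differ in the first, second and fourth rows on the oxygen clock, and still differ in the second and fourth on the more favourable clock.

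**Step 3. Illustration.** Assume an exponential time from start of protocol to birth with median *m*, the same in both arms, and oxygen started at time zero. The share born before *t* minutes is 1 − 2^(−t/m).

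| Assumed median *m* | Before 5 min (no oxygen-arm data) | Before 10 min (control window incomplete) | Before 15 min (oxygen window incomplete) |
|---|---|---|---|
| 20 min | 1 − 2^(−5/20) = 15.9% | 1 − 2^(−10/20) = 29.3% | 1 − 2^(−15/20) = 40.5% |
| 30 min | 1 − 2^(−5/30) = 10.9% | 1 − 2^(−10/30) = 20.6% | 1 − 2^(−15/30) = 29.3% |
| 45 min | 1 − 2^(−5/45) = 7.4% | 1 − 2^(−10/45) = 14.3% | 1 − 2^(−15/45) = 20.6% |

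Incomplete windows are thus about 6 to 11 percentage points more common in the oxygen arm (20.6 − 14.3 to 40.5 − 29.3). If oxygen starts 5 minutes late, the oxygen-arm figures rise to 50%, 37% and 27%.

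**Step 4. Women never given oxygen.** The rate is not stated. At an assumed 5%, 10% or 20%, this is about 4, 8 or 16 of 81 women per arm (162 randomised 1:1, the total under Sample size calculation), or about 3, 6 or 12 of 58 (116, the total in the Abstract).

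**Step 5. Effect of a common window.** With the same window from the same time zero, and time to birth unaffected by allocation, the incomplete shares are equal in expectation. For medians of 20 to 45 minutes they are 29% to 14% in both arms for 0–10 minutes, or 41% to 21% in both arms for 5–15 minutes.

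**The case against.** The strongest reply is that this is an ambiguity and not a stated exclusion. The same section also anchors the oxygen arm to the start of the study protocol, which would give an untreated woman a window. The windows are introduced for the own-control analysis, so their use in the between-arm comparison is inferred. No sentence says untreated women are dropped. The start-to-birth comparison does not need oxygen to have been given. The full protocol may hold further rules.

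Much of this stands. A reader might infer that untreated women have no primary outcome at all, that fast labours are lost from the oxygen arm only, or that intention-to-treat is defeated. The document does not support those statements: there is a second anchor, and controls born before 10 minutes also have an incomplete window.

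A reader might also turn the 16% to 7% into a type I error. Multiplying by an assumed one-SD (50-point) difference for fast labours gives a bias of 8.0 to 3.7 points, against a standard error of 50 × √(2/81) = 7.9, and a type I error of roughly 17% to 8%. The arithmetic is right, but the one-SD difference has no source in the article and every control counterpart is assumed to be retained. Births within 5 minutes are also not the same group as women never given oxygen. Assuming instead that only births within 2 minutes are lost (about 7% to 3%) gives 7.1% to 5.4%. These figures show how much depends on the assumptions. They do not estimate the bias.

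The reply does not remove the core. The article's reason for choosing the periods is the contrast of oxygen with no treatment, so carrying them into the between-arm comparison is the natural reading. The anchor at the start of the protocol still leaves oxygen-arm births before minute 5 with no post-start data while controls keep a partial window. The start-to-birth comparison is supplementary and, by the authors' own account, open to influence from other interventions.

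**Conclusion.** The point holds as a badly fixed definition of the primary-outcome window. As worded, the oxygen arm's after period depends on an event the plan expects not always to happen, and the intention-to-treat outcome is then undefined. On the more favourable reading, loss of outcome through fast labour remains unequal between arms: complete loss before minute 5 in the oxygen arm only, and incomplete windows up to minute 15 against minute 10.

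Bias in the randomised comparison is possible. Its direction and size cannot be derived from the article. The illustrative shares (16% to 7% born before minute 5; about 41% to 21% against 29% to 14% incomplete) rest on an assumed exponential time to birth with a median of 20 to 45 minutes, the same in both arms, and on oxygen starting at time zero. This is a cheap and worthwhile correction, not evidence that the trial's comparison is invalid.

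**What to change.** For the intention-to-treat comparison of FHR outcomes:

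1. Define time zero in both arms as the recorded time of randomisation (envelope opened).
2. Use the same post-randomisation window for every randomised woman, whether or not oxygen was started.
3. When birth cuts the trace short, apply one rule in both arms: use the trace available up to birth. A window opening at time zero leaves fewer women with no data than one opening at minute 5.
4. Keep the 5–15 minute window counted from oxygen initiation as a secondary analysis, labelled as describing the response to oxygen actually given.
5. Optionally, add a sensitivity analysis that gives the worst rank in the Mann-Whitney test to women in either arm with no analysable trace after randomisation.

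The cost is a change of wording and one extra time on the case report form; the tracings are already digital. The downside is slight dilution of the estimated effect, because untreated or late-treated women, and any minutes before oxygen could act, count in the oxygen arm. Treatment of the women is unchanged.

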**Fig. 2 Fig2:**
[figure not shown]
The time frame of interest for analysis of outcome measures where patients serve as their own control: the control group. bpm, Beats per minute; CTG, Cardiotocogram

**Fig. 3 Fig3:**
[figure not shown]
The time frame of interest for analysis of outcome measures where patients serve as their own control: the intervention group

These periods are established because during this period, maternal hyperoxygenation can be compared with no treatment. Furthermore, we will also compare the periods from the start of the study until birth, although these results may be influenced by other interventions that may have been applied.

#### Other study endpoints and parameters

Other study endpoints and parameters to be recorded are duration of the second stage of labour, duration of time for which supplemental oxygen was received, baseline characteristics (infant sex, gestational age and birth weight, maternal age and parity).

### Hypothesis

We hypothesise that maternal hyperoxygenation will improve FHR, without any severe maternal side effects. We do not expect a difference in rates of vacuum-assisted delivery or secondary caesarean sections or in Apgar scores or umbilical cord pH values, owing to the relatively small sample size. Furthermore, we expect larger concentrations of MDA in the intervention group than in the control group.

### Handling and storage of data and documents

Data will be handled anonymously, and we will adhere to the Dutch Personal Data Protection Act. A secured subject identification code list will be used to link a study number to a patient’s name and date of birth. This file is password-protected and available only to the main investigator ([name]). All other information will contain only the study number and no data directly referring to the patient. Foetal blood gas values will be stored in the neonates’ hospital charts because this is part of conventional care. Laboratory results regarding markers for free oxygen radicals will be coded and will therefore be anonymous. All data will be stored for 15 years in accordance with good clinical practice guidelines.

### Statistical analysis

#### Sample size calculation

The study consists of two study groups: one group with suboptimal FHR patterns and one group with abnormal FHR patterns. We aim for the study to have 80% power and a level of significance of 0.05 in both groups. In one small, non-randomised study, a reduction in FHR decelerations (type II dips) of 50–100% was noted. Our present study is the only one to report FHR changes as a result of maternal hyperoxygenation. On the basis of available literature, we expect ≥ 50% improvement in the oxygen group and 0% in the control group in both suboptimal and abnormal FHR patterns [28]. We estimated a mean improvement of 50% with an SD of 50% in each group. A power analysis performed in G*Power 3.0.10 (Kiel University, Kiel, Germany) for a two-tailed Mann-Whitney *U* test (assuming that data will not be equally distributed) resulted in a sample size of 67 patients in each study group. We added an extra 20% to compensate for missing data. Because we have two separate study groups (suboptimal and abnormal FHR group), we need 162 patients to participate.

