### Patient recruitment and randomisation

All patients eligible to be included in this study will be asked antepartum to participate when they visit the outpatient clinic or when they are admitted to the delivery ward. All patients will receive oral and written information about the study from the attending midwife or doctor or from a co-investigator (Additional files 2 and 3). After informed consent is obtained, and only in case of suboptimal or abnormal FHR patterns during the second stage of labour, randomisation is performed using sealed opaque envelops. The allocation sequence is computer-generated using random blocks of four or six patients.

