In this study, we focus on the foetal condition during the second stage of labour and short-term neonatal outcome. This implies that abnormalities in FHR patterns during the first stage of labour are not taken into account. We believe that the randomisation process will limit its influence. With regard to the neonatal period, we did not arrange long-term follow-up, because we do not expect any clinically relevant side effects that can be attributed to maternal hyperoxygenation. Besides, the sample size is too small to draw firm conclusions on long-term neonatal effects in this study.

Power analysis of the present study is based on the expected effect on the primary outcome measure, and the study is not powered to find any significant differences in Apgar score and umbilical cord blood gas values. In the power analysis, we used an expected improvement in deceleration depth and duration of 50%. On one hand, this value is based on small non-randomised studies and may be overestimated. On the other hand, those studies provide the only available data. Also, we believe it is unlikely that a limited improvement in deceleration depth and duration has clinical relevance. The sample size is calculated for each of the subgroups of suboptimal and abnormal FHR tracings. We believe it is important to assess the effect of the intervention in these subgroups because foetuses with lower initial pO_2_ levels may profit more from maternal hyperoxygenation [29].

Regarding the subgroups of AGA and SGA infants, we did not increase our sample size to reach an adequate number of participants in the SGA group. Nevertheless, we find it interesting to investigate whether there is a different effect of maternal hyperoxygenation in SGA infants compared with AGA infants.

Because of organisational challenges, it is not possible to conduct a double-blind trial. Hence patients and delivery room staff are not blinded to the patient’s allocation to a study group, which may lead to observer bias. However, analysis of FHR tracings will be done using a computerised algorithm, to minimise bias, and the investigators judging the CTGs and secondary outcome measures are blinded to the study arm.

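### Each FHR category gets its own full 0.05 and a combined analysis is added, but the plan does not say which of the three decides its single question

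*Protocol article*

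**What the plan says.** Under Sample size calculation, the article defines its groups by FHR pattern, not by treatment arm: "The study consists of two study groups: one group with suboptimal FHR patterns and one group with abnormal FHR patterns". It then sets the operating characteristics for each: "We aim for the study to have 80% power and a level of significance of 0.05 in both groups". The Discussion confirms that the size was worked out per subgroup and gives the reason: "We believe it is important to assess the effect of the intervention in these subgroups", because fetuses that start with poorer oxygenation might gain more.

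Under Data analysis: "Outcome measures will be calculated for the combined group and the subgroups of suboptimal and abnormal FHR tracings". SGA and AGA subgroups follow. No analysis is called primary, and no order or division of the significance level is given. The only remark on adjusting alpha is under Interim analysis and concerns the safety look.

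Against these several analyses stand one general expectation of better FHR (Hypothesis) and one decision at the end of the Discussion: no FHR improvement means the treatment should not be used, and a benefit leads to a multicentre trial.

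On allocation, the article says: "The allocation sequence is computer-generated using random blocks of four or six patients". It does not mention FHR category there.

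**The concern.** Three things do not fit together.

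- **Error rate.** Two categories and the combined group can each produce a significant result, and the plan does not say which one answers the single question. If any of them may, the trial's error rate is not the 5% that a reader will assume.
- **Power.** The 80% is promised per category, but it depends on how many women fall into each. The total fixes only the sum.
- **Differential effect.** The categories exist because the effect may differ between them. A p-value in each does not address that. One significant and one non-significant category is compatible with the same effect in both.

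At stake is whether a positive report can be read at its nominal level, and whether a contrast between categories would be taken for effect modification.

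**Working it through.** **Inputs.** From Sample size calculation: two-sided alpha 0.05 and 80% power in each category, and a Mann-Whitney test. For the effect: "we expect ≥ 50% improvement in the oxygen group and 0% in the control group in both suboptimal and abnormal FHR patterns" and "We estimated a mean improvement of 50% with an SD of 50% in each group", so d = 50/50 = 1.0. Also 67 per category, 20% added, 162 in total. Assumed by me: 1:1 allocation, an asymptotic efficiency of 3/π = 0.955 for Mann-Whitney against the t test, and the category shares, since the article gives no case mix.

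**The plan's own figure.** 67 × 1.2 = 80.4, rounded up to 81, and 2 × 81 = 162. The total therefore presumes 81 women in each category, or 67 + 67 = 134 analysable. The 67 itself does not follow from d = 1.0: the t test needs 16.71 per arm, and 16.71/0.955 = 17.5, so 18 per arm or 36 per category. The value 67 appears as a per-arm number at d = 0.5 (63.77/0.955 = 66.8). That is a separate problem, as is the total of 116 in the abstract. I keep 134 here because it is what the sample size section implies.

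**Error rate.** The categories contain different women, so their tests are independent:

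- Two categories at 0.05: 1 − 0.95² = 0.0975.
- Adding the combined test, with z_comb = √s·z₁ + √(1−s)·z₂ and s the share of one category (2,000,000 simulated draws): 11.5% at s = 0.5, 11.4% at 0.7, 11.2% at 0.8.
- To hold 5% over all three at s = 0.5, each test would need about 0.020.

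**Power in the smaller category.** Per-arm n = 134 × share / 2, multiplied by 0.955 and entered in the two-sided t-test power at alpha 0.05, d = 1.0:

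| Share (assumed) | Per-arm n | Power |
|---|---|---|
| 50% | 33.5 | 98% |
| 30% | 20.1 | 85% |
| 25% | 16.75 | 78% |
| 20% | 13.4 | 68% |

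The limit for 80% is 36 women, and 36/134 = 27%.

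**Differential effect.** Suppose the true effect is identical in both categories, split 50:50. The chance that exactly one is significant is 2 × power × (1 − power). At d = 1.0 this is 2 × 0.976 × 0.024 = 5%. At d = 0.5 (an assumption; the Discussion concedes that the expected effect may be too large) it is 2 × 0.504 × 0.496 = 50%. A direct comparison has standard error √(4/(33.5 × 0.955)) = 0.354 SD, so a 95% interval of about ±0.69 SD. Its power is about 29% for a difference of 0.5 SD and 81% for 1.0 SD.

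**Price of adjustment at d = 1.0.** At 50:50, power per category at alpha 0.025 is 95.3%. Under Holm, with the same effect in both, it is 0.953 + (0.976 − 0.953) × 0.953 = 97.5%. At 18 per arm it is 81% if the larger category is rejected first and 72% if it is not. A combined test with 67 per arm has 80% power even at d = 0.5.

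**The case against.** The best defence is that the categories are two pre-specified questions, each with its own conclusion, for which 0.05 each is acceptable. That would stand if the article drew a conclusion per category. Instead it states one hypothesis and one decision. It is also true that the combined analysis is only said to be calculated; its use at 0.05 as a further route to success is my assumption, and the 11.5% depends on it.

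Four stronger readings are tempting, and the document does not support them.

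- **That per-category power holds only at an even split.** On the stated d = 1.0 it does not fail until the smaller share drops below about 27%.
- **That randomisation ignores category and no quota exists.** The article is silent on both. It is a condensed account, and a full protocol is available on request. A per-category target is stated; only the means of reaching it is not.
- **That the error rate is higher still because depth and duration of decelerations are both named in the primary outcome.** The article does not say that they are tested separately and gives no correlation between them. That is a question of endpoint definition.
- **That the plan will misreport a differential effect.** This is a risk, not an error already made, and an interaction analysis may be set out elsewhere. A formal test would also have low power for moderate differences, so an estimate with its interval is more useful than a p-value.

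**Conclusion.** The concern holds in a limited form. The text gives each category a full 0.05 and 80% power, adds a combined analysis, and leaves open which result answers the one question posed. If any one of them suffices, the false-positive risk is 9.75% for the two categories and about 11.5% with the combined test at 0.05.

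Per-category power depends on a case mix that the article neither states nor secures. At the stated effect, moderate imbalance is tolerable and shares below about 27% are not. These figures assume 134 analysable women, 1:1 allocation and d = 1.0, and the shares are illustrative. The planned category results, taken alone, cannot support the differential effect that motivates them.

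This should be settled before analysis. It does not invalidate the design.

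**What to change.** Before the outcome data are analysed by arm, record one of two choices:

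1. **Preferred.** One confirmatory between-arm test in all randomised women at two-sided 0.05, stratified by FHR category at randomisation (van Elteren, or category as a covariate). Report the category results as secondary, with a treatment-by-category estimate and its confidence interval.
2. **If both categories must stay confirmatory.** Apply Holm across the two and label the combined analysis supportive.

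In either case, state per-category power as conditional on the category mix.

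The practical cost is small: no new data and no change to recruitment. It is nonetheless a real decision about the primary analysis and should be documented as one. Option 1 gives up a stand-alone, unadjusted 5% claim in a single category. Option 2 costs little power at the stated effect with an even split (98% falls to between 95% and 97.5%), and more if one category is small and the other shows nothing. I would not ask for separate envelope sequences: recruitment was due to end on 31 March 2018 (Trial status), so little or no enrolment would be affected.
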